### Randomization, allocation concealment and blinding

After enrollment, eligible participants will be assigned to either the control group or intervention group in a ratio of 1:1 (500 in each). Two stratification factors, each at two levels, will be used: age (≤ 40 years, > 40) and daily cigarette consumption (≤ 20 pack-years, > 20). A random permuted block sizes of 2, 4, or 6 will be used to achieve similar numbers of participants in both the intervention group and the control group.

Allocation concealment can be guaranteed as the random number sequence will be generated by a biostatistician who is not a member of the research team, and the random number sequence will be kept secret from researchers who are responsible for the recruitment.

As the interventions in two groups cannot be completely blinded in this study, this RCT will be single-blind in which all outcome assessors and data analysts will be blind to group allocation.

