### Statistical analysis

Upon completion of data collection, data will be cleaned and prepared for data analysis. Primary and secondary outcome variables will be checked for distribution, outliers, and missing patterns, and appropriate steps will be taken where necessary. All analysis will be conducted through SAS 9.4. Baseline demographics and smoking-related characteristics will be summarized and presented. Continuous variables (e.g. age) will be presented as numbers observed, means, and standard deviations. Categorical variables (e.g. marital status) will be presented as frequencies and percentages.

The main analysis will be focused on the comparison of smoking cessation rates in the intervention and control groups. This involves a comparison of the primary outcome variables and some secondary outcome variables including 7-day point-prevalence abstinence and self-reported continuous abstinence at each follow-up point. Independent t-tests and χ^2^ tests will be used to detect differences between the two groups depending on the type of variables. Logistic regression will be explored to assess group differences after adjusting for any baseline demographic or clinical characteristics that showed significant differences and variables that have been reported to be associated with smoking cessation [39].

Our analysis will be conducted based on intention-to-treat (ITT) principle and participants who are lost to follow-ups will be considered as continuing smokers with no reduction in cigarette consumption compared with baseline. The results from the analysis using the Multiple Imputation and Last Observation Carried Forward approaches to process missing data and per-protocol analysis will be conducted as sensitivity analyses. Subgroup analysis by baseline characteristics on quitting outcomes will be conducted by interaction terms.

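### The exploratory adjusted logistic model takes in covariates because they differ significantly at baseline, so its content depends on chance, and nothing guarantees that it contains the stratification factors

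*Protocol article*

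**What the plan says.** Three statements in the protocol article bear on this point.

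- Statistical analysis, main comparison: "Independent t-tests and χ^2^ tests will be used to detect differences between the two groups depending on the type of variables". No covariate or stratification factor is attached to these tests.
- Statistical analysis, adjusted comparison: "Logistic regression will be explored to assess group differences". Covariates come in by two routes joined by an *and*. The first is "adjusting for any baseline demographic or clinical characteristics that showed significant differences"; the second is "variables that have been reported to be associated with smoking cessation", with a literature reference. No variable is named under either route.
- Randomization, allocation concealment and blinding: "Two stratification factors, each at two levels, will be used: age (≤ 40 years, > 40) and daily cigarette consumption". Allocation is "in a ratio of 1:1 (500 in each" arm), and "A random permuted block sizes of 2, 4, or 6 will be used".

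The Statistical analysis section does not name age group or cigarette consumption as terms in any comparison between the arms.

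**The concern.** Under concealed randomisation, any baseline difference between the arms is due to chance. A p-value for that difference says nothing about whether the variable predicts quitting, which is the reason to adjust. The first route can therefore admit variables with no prognostic value, and it leaves the model unknown until the data have been seen.

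This matters more for a logistic model than for a linear one. An odds ratio depends on which covariates are conditioned on, even without confounding, so two realisations of the same trial could report adjusted odds ratios that estimate different quantities. This regression is the only covariate-adjusted estimate of the app's effect that the section describes.

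The first route also works against the design. Stratified blocks are meant to keep the arms balanced on age group and consumption. A rule that waits for imbalance will pass over the very factors that the investigators thought important enough to stratify on.

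**Working it through.** **Sample size, to see whether it depends on the rule.** Inputs from Sample size and power calculation: 13.1% against 6.4%, two-sided 5%, 80% power, 35.8% loss.

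- Pooled formula, mean proportion 0.0975: n = [1.960 × √(2 × 0.0975 × 0.9025) + 0.842 × √(0.131 × 0.869 + 0.064 × 0.936)]² / 0.067² ≈ 307 per arm. The unpooled form gives 304. The stated 309 is reproduced closely.
- Loss to follow-up: 309 / (1 − 0.358) = 481.3, stated as 481.
- The calculation compares two proportions without covariates, so no sample-size figure turns on the covariate rule.

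**Chance that the first route adds a covariate by luck.** For k independent baseline variables, each tested at 5%, the chance is 1 − 0.95^k. The article states neither k nor the test level; both are assumptions, as is independence.

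| k | 5 | 8 | 10 | 15 | 20 |
|---|---|---|---|---|---|
| Chance of at least one | 23% | 34% | 40% | 54% | 64% |

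**Would the first route pick the stratification factors?**

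- Bound: with blocks of at most 6, an unfinished block leaves an imbalance of at most 3 in a stratum. One level of a factor spans two of the four strata, so its imbalance is at most 6. With 500 per arm the difference in proportions is then 6/500 = 0.012. At an assumed prevalence of 25% the standard error is √(0.25 × 0.75 × 2/500) = 0.027, so z is about 0.44, far below 1.96.
- Simulation: 3,000 trials of 1,000 participants, four strata, random blocks of 2, 4 or 6, assumed prevalences of 40% and 25%. Neither factor was ever significant (largest |z| 0.29). A factor not used in stratification was significant in 5.2% of trials.

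**Does the rule harm the test?** Simulation of 3,000 trials of 1,000 participants under each of no effect and 6.4% against 13.1%. The prognostic effects are assumed: log odds ratios of 0.5 and 0.4 for the stratification factors, and 0.3, 0.3, 0.2, 0.2, 0.1 and five zeros (per standard deviation) for ten others. Allocation used blocks of 2 within strata.

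| Model | Type I error | Power |
|---|---|---|
| Unadjusted | 4.5% | 94.6% |
| Covariates selected by baseline significance | 4.5% | 94.7% |
| Pre-specified: both stratification factors and the five prognostic covariates | 4.7% | 95.6% |

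The Monte Carlo standard error near 4.5% is √(0.045 × 0.955 / 3000) = 0.4 points, so the type I error rates are indistinguishable. The power difference is 95.6 − 94.7 = 0.9 points. In the no-effect runs 60.1% of trials selected no covariate, in line with 0.95^10 = 59.9%. The middle row applies the first route alone; the article's literature route could recover some of the 0.9 points.

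**The case against.** The strongest reply is that the rule has a second half. Predictors known from the literature enter whatever the observed balance, so prognostic adjustment is part of the plan. Age or consumption may well be among them; the cited source is not available here, so it cannot be said that they are left out. A full covariate list is also something that a condensed article may leave to an analysis plan. All of this stands, and for that reason the lack of a list is not the point. What remains is that the significance rule is stated outright, and that the second route adds variables without removing those that chance has put in.

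The regression is also described as exploratory and follows the unadjusted tests. That stands too. A reader might infer that the primary comparison is compromised; it is not, because the χ² test involves no covariate selection.

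The 40% figure rests on an assumed number of independent variables, while baseline smoking measures are likely to be correlated. It measures how often the model changes by luck, not bias or error.

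Finally, the near-zero chance of selecting the stratification factors applies to them as dichotomised. If age were tested as a continuous variable, it could still differ by chance within strata and be selected.

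**Conclusion.** The point holds in a limited form. The protocol article fixes a poor rule for an exploratory analysis: part of the adjusted model is chosen by chance imbalance, and its odds ratio is therefore not defined in advance. The randomisation factors would almost never enter by that route in their dichotomised form, and their entry by the other route is possible but not assured.

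Two stronger readings are not supported. One is that selection by imbalance distorts the error rate: under the assumed effects it was 4.5% with selection and 4.7% with a pre-specified model, so no inflation is shown. The other is that the plan throws away the precision of prognostic covariates: they are expressly included by the second route, and the difference at stake was about 1 point of power even with that route ignored. These simulation results depend on the assumed prognostic strengths. The objection to a data-dependent model does not.

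**What to change.** In Statistical analysis, delete the phrase that makes a significant baseline difference the ground for adjustment, and state that no covariate will be selected by a baseline significance test. Specify the adjusted logistic model before the data are seen, with its terms included whatever the observed balance:

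- arm;
- the two stratification factors as actually randomised, namely age group and the cigarette-consumption factor;
- a named list of literature-based predictors collected at baseline. FTND can be on it if the body of Table 1, which is not shown here, confirms that it is a baseline measure; only its footnote is visible.

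The consumption factor must first be reconciled in the randomisation section, which calls it daily consumption but states its cut-off of 20 in pack-years. The model should use whichever variable the randomisation system actually used.

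The cost is a sentence or two of text. Sociodemographic characteristics and smoking history are already collected at prescreening, and no sample-size figure changes.

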### Sample size and power calculation

The proposed sample size is based on the primary outcome of self-reported 6-month continuous abstinence. Based on a meta-analysis conducted by Ybarra [26], the 6-month continuous abstinence for mobile phone-based smoking cessation intervention is 13.1%, compared with 6.4% in the control group. To detect a 2-sided significant difference between groups with a power of 80% and significance level of 5%, 309 participants in each arm are estimated to be required. Considering a 35.8% loss to follow-up in one study concerning SSC APP conducted in China [27], the final minimum sample size is 481 per group. Eventually, we set a target sample size at 1,000 people to cover the minimum sample size.

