### Follow-up and data collection

Participants in both groups will be followed up for 6 months and receive electric follow-up questionnaires sent by the WeChat Official Account 1 month, 3 months, and 6 months after enrollment. SMS will be used to remind them to complete the questionnaires on time. Non-responders will receive up to 3 additional reminder messages or calls within 1 week following the initial invitation. Compensation will be paid to improve their willingness to respond and remain in this study. When the follow-up finishes, participants in both groups will be acknowledged for their participation and participants in the control group will be referred to our SSC APP if they have not quit smoking.

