### Outcomes and measures

#### Primary outcome and measures

As we explained before, our SSC APP includes motivational protocols for those not ready to decide on a target quit date. In this study, we intend to explore the efficacy of the SSC APP as a whole, so the follow-up in this study will be tied to the date of intervention initiation. 6-month continued abstinence is selected as the primary outcomes. Considering there is no close contact or interaction between participants and the study team, biochemical verification may be infeasible as the SRNT guidelines have suggested [35], it will be self-reported. 6-month continued abstinence will be defined using the Russell 6 Standard [36] but without biochemical verification (i.e., tolerate fewer than five incidents of smoking from the quit date) and will be measured through the question “Have you smoked at all since (date of the start of the continuous abstinence period) ? A: No, not a puff; B: 1–5 cigarettes; C: More than 5 cigarettes.”

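### LOCF is planned as a missing-data sensitivity analysis with no outcome excluded; for 6-month continuous abstinence it would substitute a shorter, easier endpoint and cannot test the missing = smoking result

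*Protocol article*

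**What the plan says.** All references are to the protocol article.

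- **Primary outcome and measures:** "6-month continued abstinence is selected as the primary outcomes". The definition follows the Russell Standard without biochemical verification and allows a limited number of lapses ("tolerate fewer than five incidents of smoking from the quit date"). Follow-up is timed from the start of the intervention, not from the quit date.
- **Follow-up and data collection:** questionnaires are sent "1 month, 3 months, and 6 months after enrollment".
- **Statistical analysis, main rule:** "participants who are lost to follow-ups will be considered as continuing smokers with no reduction in cigarette consumption compared with baseline".
- **Statistical analysis, robustness:** the next sentence states "Multiple Imputation and Last Observation Carried Forward approaches to process missing data and per-protocol analysis will be conducted as sensitivity analyses". It does not say which outcomes each method covers. The same section also plans to compare continuous abstinence at each follow-up point, so an interim continuous-abstinence status will exist.
- **Sample size and power calculation:** the planning rates are given as "intervention is 13.1%, compared with 6.4% in the control group". The inflation for loss rests on one earlier study: "Considering a 35.8% loss to follow-up in one study concerning SSC APP conducted in China".

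**The concern.** LOCF needs an earlier measurement of the same quantity. Six-month continuous abstinence has none, because an answer at month 1 or month 3 cannot contain six months of abstinence. What can be carried forward is an interim status over a shorter period. Participants need only intend to quit within a month of enrolment, so an abstinent answer at month 1 may cover only a few days.

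Carrying that status to month 6 assumes that nobody relapses after the last contact, and relapse is what the endpoint is meant to capture. The article itself expects relapse during follow-up (Secondary outcomes and measures) and expects drop-out to be more likely at the later follow-ups (Compensation). Many lost participants will therefore have an early answer available to carry.

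At stake is the meaning of the sensitivity analysis. If LOCF agrees with the main result, the agreement reassures falsely. If it disagrees, nobody can tell whether the cause is missing data or the change of endpoint.

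**Working it through.** **Inputs from the article.** Planning rates 13.1% and 6.4% (difference 13.1 − 6.4 = 6.7 points); two-sided 5% level, 80% power; 309 per arm, inflated for 35.8% loss to 481; 500 per arm randomised; questionnaires at months 1, 3 and 6.

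**Step 1. The plan's own figures.** The two-proportion formula with pooled variance gives 307 per arm, against 309 stated. Inflation: 309 / (1 − 0.358) = 309 / 0.642 = 481.3, against 481 stated. Both reproduce closely enough, so 35.8% is used below as the plan's anticipated loss.

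**Step 2. Number affected.** 500 × 0.358 = 179 participants per arm without a month-6 answer; 500 × 0.642 = 321 with one.

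**Step 3. What LOCF does to them.** A last status of smoking gives failure, as under missing = smoking. A last status of abstinent gives success, with 6 − 3 = 3 or 6 − 1 = 5 months unobserved. Let q be the share of *all* lost participants who were abstinent at last contact; anyone lost before the month-1 answer counts as not abstinent. Then

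LOCF rate = missing = smoking rate + 0.358 × q.

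The article does not give q, so a range is shown:

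| q (assumed) | Added to the arm's rate | Participants per 500 |
|---|---|---|
| 5% | 0.358 × 5% = 1.8 points | 9 |
| 10% | 3.6 points | 18 |
| 20% | 7.2 points | 36 |
| 30% | 10.7 points | 54 |

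**Step 4. Effect on the comparison.** Assume that 13.1% and 6.4% hold among completers and that loss is 35.8% in both arms. Missing = smoking gives 0.642 × 13.1% = 8.4% and 0.642 × 6.4% = 4.1%: difference 4.3 points, risk ratio 2.05. LOCF then gives:

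| q, APP vs control (assumed) | LOCF rates | Difference |
|---|---|---|
| 20% vs 20% | 15.6% vs 11.3% | 4.3 points (risk ratio 1.38) |
| 20% vs 10% | 15.6% vs 7.7% | 7.9 points |
| 10% vs 20% | 12.0% vs 11.3% | 0.7 points |

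With equal loss and equal q the difference is unchanged and only the ratio shrinks. With unequal q the difference can nearly double or nearly vanish, although the month-6 data are the same in every row.

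**Step 5. No difference at 6 months.** Assume 6.4% among completers in both arms, q of 20% vs 10%, and that nobody carried forward stays abstinent. The true rates are then equal (4.1% in each arm), but LOCF compares 11.3% with 7.7%. At 500 per arm that comparison is significant about 49% of the time. This is a deliberately unfavourable case. It shows what the LOCF result responds to: early abstinence among people who later drop out.

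**The case against.** **Scope.** The LOCF sentence names no outcome, and several secondary outcomes (cigarettes per day, quit attempts, 7-day abstinence) do have earlier values to carry. The authors may intend LOCF only for those. This stands as a limit: use on the primary outcome is the plain reading, since the sentence directly follows the rule for missing abstinence and excludes nothing, but it is not spelled out.

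**No earlier value at all.** A reader might infer that nothing exists before month 6 to carry forward. That goes too far, because continuous abstinence is to be compared at each follow-up. The interim status exists; it measures a shorter period.

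**Size of the inflation.** A reader might also infer that LOCF must give an implausibly high abstinence rate. The documents do not support this. Suppose true abstinence is 10% and completers also show 10% (assumed). Missing = smoking gives 0.642 × 10% = 6.4%, and LOCF gives 6.4% + 0.358 × q. That exceeds 10% only if q exceeds 10%; at q = 5% it is 8.2%, below the truth. Even at q = 25% it is 15.4%, not far from the 13.1% planned for the intervention arm.

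**False benefit from unequal loss.** Take no effect, 10% abstinent among completers, q = 25%, and loss of 40% in the APP arm vs 30% in the control arm (all assumed). LOCF gives 0.60 × 10% + 0.40 × 25% = 16.0% vs 0.70 × 10% + 0.30 × 25% = 14.5%. That 1.5-point excess has z of about 0.66 at 500 per arm and would change no conclusion. Missing = smoking gives 6.0% vs 7.0% in the same case, a false 1-point harm of similar size. Sensitivity to unequal loss is therefore not peculiar to LOCF.

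**Weight.** LOCF is one of three sensitivity analyses, and the primary result does not rest on it. This also stands. None of these points makes LOCF a valid check on 6-month continuous abstinence.

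**Conclusion.** The concern holds, limited to LOCF on continuous abstinence. As written, the plan allows an answer from month 1 or 3 to be scored as six months of abstinence. LOCF then answers a different question and cannot show whether the missing = smoking result is robust.

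The inflation per arm is 0.358 × q, so with q between 5% and 20% it runs from about a quarter of the planned 6.7-point difference (1.8 / 6.7 = 0.27) to slightly more than all of it (7.2 / 6.7 = 1.07). These figures rest on the 35.8% loss that the article borrows from another study and on assumed values of q. The difference between arms is distorted only if q or loss differs by arm, in a direction that cannot be stated in advance.

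A reader should not conclude that the missing-data plan as a whole fails, or that LOCF is bound to favour the APP. The main analysis and the multiple imputation analysis are unaffected. The point is worth correcting before analysis because a named sensitivity analysis is likely to be carried into the analysis plan and reported.

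**What to change.** - State that LOCF will not be used for continuous abstinence, and say to which outcomes, if any, it still applies.
- Keep missing = smoking as the main analysis and multiple imputation as a sensitivity analysis.
- In place of LOCF, add a delta-adjusted (pattern-mixture) analysis of 6-month continuous abstinence. It varies the odds of smoking in lost versus observed participants, separately in each arm, up to the point where the conclusion changes. The reader can then judge whether that point is plausible.

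Cost: one sensitivity analysis is exchanged for another, with some extra programming. No new data, visits or participants are needed.

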### Ethics approvals and dissemination

Ethics approval (reference number: 202204) was obtained from the Ethical Review Committee of the Chinese Center for Disease Control and Prevention. Informed consent will be obtained from all the participants electronically. Results are expected to be published in peer-reviewed journals and presented at conferences.

### Safety

As most nicotine withdrawal symptoms are moderate and will subside within several weeks, we believe that this intervention is barely harmful to any participants. In case some participants experience any severe physical or mental withdrawal symptoms, professionals from the Chaoyang smoking cessation clinic will be available at any stage. Serious symptoms occurred will be recorded and reported.

### Confidentiality

The company responsible for software operations will sign a confidentiality agreement and complete the cyber security evaluation to avoid any data breach. All study-related data will be exported and stored securely on the research team’s encrypted computer under a coded identification number to maintain participant confidentiality. All data that contain personal identifiers, such as screening data for eligibility and informed consent forms, will be stored separately from study records identified by a code number. Only the principal investigator and research assistants will have access to the study data.

## Discussion

In recent years, SSC APPs have been booming worldwide. Hundreds of SSC APPs are circulating in the APP market on platforms like Google play and the Apple store, and they have attracted tremendous downloads [40, 41]. However, most APPs are not based on relevant scientific theories and there is little scientific evidence from randomized controlled trials on the impact of these APPs, especially in China, where no validated smoking cessation APP is publicly available now [40, 42]. Furthermore, due to the different cultural contexts, effective SSC APPs in foreign countries may not be well-worked in China [22].

This study will help us to evaluate the efficacy of an individual-tailored smoking cessation intervention APP developed by the Tobacco Control Office based on the BCW theory and the Transtheoretical Model. Ideally, it will help us understand how smartphones can be used to promote smoking cessation. If this APP proves to be effective, it could be integrated with the existing smoking cessation services and further facilitate smoking cessation at the population level. As a country with more than 300 million smokers, any amount of improvement could be amplified by the huge smoking population and yield considerable benefits.

As this study will be conducted online, several limitations lay ahead. First, it is unlikely to collect biochemical samples as participants are scattered remotely in various places. Thus, self-reported 6-month continued abstinence will be considered as an alternative to biochemically verified abstinence. Besides, without close contact or interaction, participants may be less likely to take this study seriously and thus more likely to be lost to follow-up. Hence, participants will be reminded through different approaches at the follow-up points and receive monetary incentives after completing follow-up questionnaires.

Overall, this study could shed some light on the efficacy of an individual-tailored smoking cessation intervention APP in China with the potential to address the existing and unmet demands of Chinese smokers. We predict this innovative study to be a promising attempt and may have major implications for smoking prevention policy and mobile health in general.

